# Study protocol for the Heads-Up trial: a phase II randomized controlled trial investigating head-up tilt sleeping to alleviate orthostatic intolerance in Parkinson’s Disease and parkinsonism

**DOI:** 10.1186/s12883-023-03506-x

**Published:** 2024-01-02

**Keywords:** Supine hypertension, Orthostatic hypotension, Syncope, Blood pressure, Feasibility, Implementation, Autonomic failure, Nocturia

## Abstract

**Background:**

In persons with Parkinson’s Disease (PD) or certain forms of atypical parkinsonism, orthostatic hypotension is common and disabling, yet often underrecognized and undertreated. About half of affected individuals also exhibit supine hypertension. This common co-occurrence of both orthostatic hypotension and supine hypertension complicates pharmacological treatments as the treatment of the one can aggravate the other. Whole-body head-up tilt sleeping (HUTS) is the only known intervention that may improve both. Evidence on its effectiveness and tolerability is, however, lacking, and little is known about the implementability.

**Methods:**

In this double-blind multicenter randomized controlled trial (phase II) we will test the efficacy and tolerability of HUTS at different angles in 50 people with PD or parkinsonism who have both symptomatic orthostatic hypotension and supine hypertension. All participants start with one week of horizontal sleeping and subsequently sleep at three different angles, each maintained for two weeks. The exact intervention will vary between the randomly allocated groups. Specifically, the intervention group will consecutively sleep at 6°, 12° and 18°, while the delayed treatment group starts with a placebo angle (1°), followed by 6° and 12°. We will evaluate tolerability using questionnaires and compliance to the study protocol. The primary endpoint is the change in average overnight blood pressure measured by a 24-hour ambulatory blood pressure recording. Secondary outcomes include orthostatic blood pressure, orthostatic tolerance, supine blood pressure, nocturia and various other motor and non-motor tests and questionnaires.

**Discussion:**

We hypothesize that HUTS can simultaneously alleviate orthostatic hypotension and supine hypertension, and that higher angles of HUTS are more effective but less tolerable. The Heads-Up trial will help to clarify the effectiveness, tolerability, and feasibility of this intervention at home and can guide at-home implementation.

**Trial registration:**

ClinicalTrials.gov NCT05551377; Date of registration: September 22, 2022.

## Background

Autonomic dysfunction is common, debilitating and often underrecognized in Parkinson’s Disease (PD) [1, 2]. The risk of orthostatic hypotension increases with age and disease duration. Up to one third of all people with PD experience orthostatic hypotension at some point during their disease course [2]. Orthostatic hypotension is also common amongst certain types of parkinsonism, especially in multiple system atrophy (MSA) with prevalence of up to 80% [3, 4]. In both PD and MSA, orthostatic hypotension is mostly neurogenic, but it may also be caused or aggravated by hypovolemia, dopaminergic drugs or other blood pressure (BP) lowering medications [1]. Orthostatic hypotension can present with orthostatic intolerance (e.g., postural light headedness), but the symptoms may also be less recognizable such as fatigue, cognitive slowing or coat hanger pain while standing. It is important to recognize and treat orthostatic hypotension as it may lead to syncope and falls with resulting injuries [5, 6]. The symptoms may also lead to a reduction in physical activity, which in turn aggravates other movement disorder symptoms such as balance and mobility problems [7], thereby increasing the risk of falling even further. Previous placebo-controlled randomized controlled trials (RCT) have shown that effective treatment of orthostatic hypotension increases physical activity [8], and improves functional mobility in people with orthostatic hypotension and PD or parkinsonism [9].

Up to half of all people with PD or MSA and orthostatic hypotension also exhibit supine hypertension [10]. Supine hypertension can be severe and last for several hours during nocturnal sleep, putting people at a higher risk for early morning hypertensive emergencies such as stroke and myocardial infarction [10–13]. Over time, the combination of the very high recumbent and very low upright BP may contribute to end-organ damage at the cerebral, cardiac and renal level [14, 15]. Indeed, among people with PD the presence of white matter lesions was associated with both supine hypertension and orthostatic hypotension [16]. Supine hypertension is also known to foster pressure natriuresis overnight thus promoting orthostatic hypotension [1, 13]. This may partially explain why orthostatic hypotension is often worse in the morning [17]. The common co-occurrence of orthostatic hypotension and supine hypertension makes pharmacological treatment very complex, as treatment of one aggravates the other [13].

A non-pharmacological and non-invasive intervention that can improve both orthostatic hypotension and possibly also supine hypertension is head up tilt sleeping (HUTS). The concept of HUTS is based on clinical observations made over 80 years ago [18–20]. These observations showed symptomatic and objective improvement of orthostatic hypotension during daytime. However, thus far HUTS has only been investigated in small and largely observational cohort studies, and never in a population with movement disorders [21–24]. The optimal tilt angle of HUTS is currently unknown but based on the presumed gravitational effect a steeper head-up tilt sleeping position is likely to be most effective, but is also less tolerable due to more discomfort in the sleeping position. The studied angles showing improved orthostatic tolerance varied from 12° to 40° [18, 19, 21–23], yet these studies did not evaluate the impact on nocturnal supine hypertension. This could be attractive, however, because from a physiological perspective, one would expect a more marked effect on supine hypertension rather than on orthostatic hypotension. HUTS will likely alleviate supine BP due to direct gravitational effects while orthostatic BP improvement is mediated by changes in extracellular fluid compartments. Accordingly, a placebo controlled RCT applying low HUTS angles (5°) found no effect on orthostatic hypotension, but more frequent occurrence of ankle oedema in the intervention group. This suggests that even a modest angle has potential to reduce supine hypertension [25, 26]. In clinical practice, HUTS is often not recommended, and when it is modest tilt angles are suggested with presumably at best also modest effects, as a guideline on practical implementation is still lacking [25, 26].

We here describe the design of the Heads-Up study, in which we investigate the potential efficacy and tolerability of different angles of HUTS as a treatment for both supine hypertension and orthostatic hypotension in people with PD. We will evaluate the effect of different angles of HUTS on several BP outcomes, orthostatic intolerance, compliance, tolerability, nocturia, as well as motor- and non-motor PD symptoms. Finally, we will explore whether certain participant characteristics may predict the effectiveness of HUTS.

## Methods

### Study design

The Heads-Up trial is a double-blind, phase II RCT. Participants will be randomized in two groups: the treatment group and the delayed treatment group (Fig. 1). It is a two-center study performed at the Radboud University Medical Center (Radboudumc) and Leiden University Medical Center (LUMC), both located in The Netherlands. The total study duration for participants is seven weeks.

**Fig. 1 Fig1:**
[figure not shown]
Overview of the trial. HUTS, head-up tilt sleeping

#### Population

We aim to include a diverse population of fifty adults diagnosed with PD or parkinsonism by a neurologist that have both supine hypertension (systolic BP of ≥ 140 mmHg, and/or diastolic BP of ≥ 90 mmHg, after 5 min of supine rest) [12] and orthostatic hypotension (systolic decrease of ≥ 30 mmHg [27] or diastolic decrease of ≥ 10 mmHg upon standing, i.e. the orthostatic hypotension criteria for those with co-existing supine hypertension) [27, 28]. Participants must experience symptoms of orthostatic intolerance (e.g., dizziness, cognitive slowing or blurry vision while standing). Participants must be able to walk, with or without walking aid, must have a stable medication regime for both supine hypertension and orthostatic hypotension during participation, and are not allowed to simultaneously participate in other intervention trials. Finally, participants are only eligible if they can adhere to the study schedule themselves or with help of support at home.

#### Recruitment

We will recruit primarily at our outpatient clinics (Radboudumc & LUMC). In addition, other neurologists, Parkinson nurses, geriatricians and internists throughout the Netherlands will be invited to refer potentially eligible patients. We will also use open recruitment via social media and the media channels of the Dutch Parkinson Patient Association and ParkinsonNext (https://www.parkinsonnext.nl/), a platform connecting people with PD and an interest in research with researchers (n > 2000).

#### Procedure

Those who expressed their interest in participating are contacted by the research team to screen for eligibility and informed about the study protocol. If BP data is unavailable, we will discuss how these measurements can be obtained (self-measurements or with help from a researcher). All participants will receive elaborative explanation on the study procedures at the start of the first in-clinic session, and prior to participation they will sign an informed consent form. During the study duration of seven weeks there will be at least seven scheduled moments of contact. Participants will perform several activities and measurements:

First, we will plan an in-clinic visit (either at the Radboudumc or LUMC). For consistency, this visit will always be scheduled in the early afternoon. Here, participants can ask additional questions and sign informed consent. The researchers will then gather baseline characteristics, perform their initial assessments with continuous BP measurements and several questionnaires. The assessments and questionnaires can be found in Table 1. Finally, the participant will be asked to install an app through which they can report their at-home measurements.After this session, the participants are randomized to one of the two groups. We will apply the randomization feature of the data management system Castor EDC with block sizes of two and four to allow the interim analysis. We will stratify based on gender. The researchers who perform the assessments and/or are involved in the analyses will remain blinded to the participant allocation during the study. Only the researchers who perform the randomization and deliver the materials at home will know which group the participants are allocated to. We will not inform the participants that we expect that the first angle in the delayed treatment group has no effect on BP regulation, making this a double-blind study.We will schedule an appointment to deliver all study materials within one week after the first session.Participants will perform daily at home measurements of supine BP and their weight. They will be asked to record their measurements in the app.We will schedule four video calls with the participants to discuss potential caveats and supervise the BP standing tests. Participants will also be asked to fill out several questionnaires in the app on this day and to disclose whether they slept in the prescribed angle. During this video check-in we will also guide the initiation of the 24-hour ABPM (Table 1).Participation ends with a follow-up in clinic session, also scheduled in the early afternoon for consistency, where the BP measurements and questionnaires from the first in clinic session are repeated and participants are asked about their experiences. When they want to proceed HUTS, they are offered to keep the materials and to do so under supervision of their primary care physician.

#### Intervention

All participants in this study are subject to a six-week intervention. They will be sleeping in a whole-body HUTS position at three different angles, for two weeks each. The treatment group will sleep at HUTS angles of 6°, 12° and 18°. The delayed treatment group will first sleep at the placebo angle of 1° which is considered the control, after which they also sleep at 6° and 12° HUTS (Fig. 1). In both groups the intervention is preceded by a week of horizontal sleeping for baseline measurements.

The necessary materials will be delivered to the participants’ homes. To facilitate implementation in the home situation we have developed a frame that can be used to tilt the mattress into all different angles (Fig. 2A). For those who do not wish to use this frame, we offer wedge shaped mattresses with similar HUTS angles (Fig. 2B). The effect of HUTS on sleep quality is not yet known, but higher angles of HUTS may cause discomfort. Slipping can be reduced by increasing the friction of bedcover fabric, placing a rolled-up towel under the hips or in several other ways. We will expand this list as participants figure out what works for them during the study. We offer to provide each participant with a sleeping partner the frame for both so that they can sleep next to each other in the same angle during the trial. For good application of the HUTS method in the participant’s home, we will pay a home visit not only to deliver the materials, but also to offer support. For those who require or request extra help during the study we will provide this by offering a telephone or video call and, if necessary, by additional home visits.

#### Testing of materials

We organized several test sessions for patient researchers to test different HUTS methods and to provide feedback on the design and usability. From these preparatory sessions we learned that it is not feasible to apply the intuitive method of blocks underneath the headboard of the participant’s bed as this is very unstable at the higher angles. The final frame (Fig. 2A) comes with a footboard to prevent participants from sliding down at the higher angles. This reduces the risk of falls from the bed during the night. We also supply handrails on the side of the bed for easier turning, as difficulties with turning is a common problem in people with PD. These handrails, together with the footboard, also form a safety barrier that prevents participants from sliding or falling out of bed and can help them get out of bed safely. For the safety of the participants, we decided to implement the highest two angles (12° and 18°) by placing the frame on the floor. We did realize that this may be problematic or even hinder participation for those who do not have the space at home for this additional frame on the floor, but we considered the alternative unsafe.

**Fig. 2 Fig2:**
[figure not shown]
Image of the HUTS method for in the participant’s home. In both situations a 12° angle is shown. **A**) The wedge-shaped mattress can be placed underneath the participant’s mattress or used separately. **B**) The frame can easily be adapted to fit to all angles that are prescribed during the study

### Outcome measures

#### Primary outcomes

##### Efficacy

The primary outcome is the home-based overnight supine BP recorded four times with the 24-hour ambulatory blood pressure measurement (ABPM). This recording will be done during one of the last three days of every phase. The measurements during the baseline horizontal week will be used to calculate the change score to determine the effect of each angle on the BP. The BP device will measure the BP every half hour during the night, according to the guidelines for ABPM measurements [29]. Participants will self-report the actual time they spend lying down in bed.

**Table 1 Tab1:** Overview of study procedures

Activity	In-clinic 1	Wk1	Wk2-3	Wk4-5	Wk6-7	In-clinic 2
Informed consent	X					
Demographics	X					
Tilt-table and BP standing test	X					X
MDS-UPDRS	X					X
Questionnaires OHQ, PSQI, FES, selected questions from SCOPA, PDQ-39, HADS and MHC-SF	X					X
Timed Up and Go test	X					X
Average overnight and daytime BP with 24-h ABPM (4x)		X	X	X	X	
Supine BP (daily, 45x)		X	X	X	X	
Standing BP (guided, 4x)		X	X	X	X	
Questionnaire on phone app (4x) - OHQ - ICIQ-N - Number of falls - Nocturia - Subjective comfort of HUTS		X	X	X	X	
Nocturia measurements - Body weight (45x) - Nighttime urine production (4x)		X	X	X	X	
Interview on barriers and facilitators of HUTS						X
**Protocol**						
Instructions	X					
Sleeping horizontally		X				
(Possible) Home visit to install angle		X	X	X	X	
HUTS angle 1			X			
HUTS angle 2				X		
HUTS angle 3					X	
Phone/video call with researcher		X	X	X	X	
Aftercare (personalized advice)						X

*BP = blood pressure; HUTS = sleeping in head-up tilt; MDS-UPDRS = Movement Disorders Society Unified Parkinson Disease Rating Scale; OHQ = orthostatic hypotension questionnaire; PSQI: Pittsburgh sleep quality index; FES: Falls Efficacy Scale; SCOPA: SCales for Outcomes in PArkinson’s disease; PDQ: Parkinson’s disease questionnaire; HADS: Hospital anxiety and depression scale; MHC-SF: Mental Health Continuum Short Form; ICIQ-N: International Consultation on Incontinence Questionnaire Nocturia Module*

##### Tolerability

We will evaluate the tolerability of HUTS with four indicators: (1) compliance, as measured by the daily question if they slept in the right angle, presented as proportion of participants that were > 80% of the study period compliant to the prescribed intervention; (2) the proportion of participants who did not tolerate the angle and returned to the previous angle; (3) the number of dropouts and if provided their reason for dropping out of the study, and; (4) reported barriers and motivators for using HUTS (evaluation during the final in-clinic session).

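### The compliance indicator pools all nights into one >80% figure per participant, so it cannot show at which angle compliance fails

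*Protocol article*

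**What the plan says.** Under Primary outcomes, the protocol article lists four tolerability indicators. The first is "compliance, as measured by the daily question if they slept in the right angle", and it is "presented as proportion of participants that were > 80% of the study period compliant to the prescribed intervention". The other three are step-backs to a lower angle, dropouts, and barriers and motivators reported at the last visit.

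On the time frame, Study design says "The total study duration for participants is seven weeks". Intervention says "All participants in this study are subject to a six-week intervention", with participants sleeping "at three different angles, for two weeks each". It adds: "In both groups the intervention is preceded by a week of horizontal sleeping for baseline measurements". The treatment group goes through 6°, 12° and 18°; the delayed group goes through 1° (placebo), 6° and 12°.

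The abstract's hypothesis is that "higher angles of HUTS are more effective but less tolerable".

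**The concern.** The hypothesis and the stated aim concern individual angles, and the article's Discussion says that the results will help choose the angles for a phase III trial. The compliance rule gives one classification per participant across all angles. Nights expected to be easy (horizontal, 1° or 6°) count the same as nights at 12° or 18°, so good adherence early on can offset poor adherence at the end.

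The article uses a separate word, phase, for the individual two-week periods, for example when it times the ambulatory recording and groups adverse events. The study period in the compliance rule therefore reads as the whole period and not as one phase. What is at stake is whether the first tolerability indicator can inform the choice of angle.

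**Working it through.** The article gives no number of nights for this rule, so there is no figure of its own to reproduce beyond the 80% threshold.

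**Inputs.** The threshold is strictly above 80%, with one answer per night (Tolerability). There are 7 weeks in total (Study design), of which 6 weeks are intervention, with 14 nights at each of three angles after 7 horizontal nights (Intervention). The article does not say whether the denominator is 49 or 42 nights, so both are shown.

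**Formulas.** The smallest passing count k is the smallest integer with k/N > 0.80. The minimum at the last angle is k minus the nights outside that angle, if all of those are compliant.

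| | N = 49 | N = 42 |
|---|---|---|
| 0.80 × N | 39.2 | 33.6 |
| Smallest passing k | 40 (81.6%) | 34 (81.0%) |
| One night fewer | 39 (79.6%), fails | 33 (78.6%), fails |
| Nights outside the last angle | 7 + 28 = 35 | 28 |
| Minimum at the last angle | 40 − 35 = 5 of 14 (35.7%) | 34 − 28 = 6 of 14 (42.9%) |
| No nights at the last angle | 35/49 = 71.4%, fails | 28/42 = 66.7%, fails |

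Reading the threshold as at least 80% leaves 40 and 34 unchanged. Table 1 lists 45 daily home measurements. If compliance were counted on those days, and if they split as 6 + 3 × 13 (an assumption), 37 days would be needed and 37 − 32 = 5 of 13 at the last angle would suffice.

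**Sensitivity to earlier misses.** With m nights missed before the last phase, the minimum becomes 5 + m (N = 49) or 6 + m (N = 42). With N = 42 and 25 of the 28 earlier nights kept (89%), m = 3 and 9 of 14 nights (64%) are needed.

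**Exposure by group.** Suppose that every horizontal and 1° night is kept. The minimum number of nights at 6° or above is then:
- N = 49: treatment group 40 − 7 = 33 of 42 (79%); delayed group 40 − 21 = 19 of 28 (68%).
- N = 42: treatment group 34 of 42 (81%); delayed group 34 − 14 = 20 of 28 (71%).

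**Same threshold per phase.** 0.80 × 14 = 11.2, so 12 of 14 (85.7%) passes and 11 of 14 (78.6%) fails. A participant with 5 or 6 of 14 nights at the last angle would be classed as non-compliant at that angle.

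**The case against.** The strongest reply is that 5 or 6 of 14 is a boundary case. It needs no missed night in the other 28 or 35, and the minimum rises quickly once there are any. This stands, and the counts should be quoted only with that condition.

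Second, tolerability by angle is also captured elsewhere. Step-backs and dropouts are indicators in their own right, comfort is asked once in each phase (Table 1), and adverse events are grouped by phase and group. This also stands. It narrows the gap to participants who keep the assigned angle nominally but skip nights. Only the daily question detects them, and the rule pools their answers.

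Third, a breakdown by angle could be left to a SAP that is not shown. This holds only in part. Nothing in the article forbids such a table, but the article itself fixes the threshold and the denominator, and they are what cause the problem.

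Fourth, no between-group test of compliance is stated, and the Final analysis section places tolerability among the exploratory analyses. A reader might infer from the exposure difference that a group comparison is invalid. The documents do not support that, because they announce no such comparison. The difference affects only how each group's percentage should be read.

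**Conclusion.** The concern holds as a limit of the compliance indicator. One pooled figure cannot locate failure by angle. It can class a participant as compliant with 36% (5 of 14) or 43% (6 of 14) of nights at the last angle, provided all other nights are compliant. The figure also represents different tilt exposure in the two groups.

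The counts assume that nights at a lower angle do not count as the right angle. The article does not say how nights after a step-back are scored. If they did count, even fewer nights at the last angle would be needed.

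Two stronger readings are tempting. One is that the rule would report good tolerability for 18°; it reports no figure for any single angle, so it cannot. The other is that a whole group using 18° on about 40% of nights would be reported as fully compliant. That would require every member to be perfect earlier and then to miss most nights without stepping back or dropping out, and nothing in the documents suggests this pattern. The overnight blood pressure analysis is not affected.

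**What to change.** State whether the study period means 49 or 42 nights. Keep the overall figure, and beside it apply the >80% rule to each 14-night phase (at least 12 of 14 nights). Report the proportion compliant by assigned angle and group, with all participants assigned to that angle in the denominator.

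For this analysis only, classify nights at a lower angle after a step-back as not at the assigned angle, and show them together with the step-back indicator. Reconcile this scoring with two places:
- the Discussion, which asks participants who do not tolerate an angle to go back to the one before;
- the Final analysis section, which puts tolerability under per-protocol principles and could therefore remove some of the people being counted.

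The step-back procedure itself is not changed.

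The cost is wording in the analysis plan. The Tolerability section says that the answers are collected daily, so no new visits, measurements or participants are needed. The downside is that the reported percentage for the highest angle will probably be lower.
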